## Abstract

**Background:**

DSM-V criteria for insomnia disorder are met by 6 to 10 % of the adult population. Insomnia has severe consequences for health and society. One of the most common treatments provided by primary caregivers is pharmacological treatment, which is far from optimal and has not been recommended since a 2005 consensus report of the National Institutes of Health. The recommended treatment is Cognitive Behavioral Therapy for Insomnia. Effectiveness, however, is still limited. Only a few studies have evaluated the effectiveness of chronobiological treatments, including the timed application of bright light, physical activity and body warming. Another opportunity for optimization of treatment is based on the idea that the people suffering from insomnia most likely represent a heterogeneous mix of subtypes, with different underlying causes and expected treatment responses.

The present study aims to evaluate the possibility for optimizing insomnia treatment along the principles of personalized and stratified medicine. It evaluates the following:The relative effectiveness of internet-supported cognitive behavioral therapy, bright light, physical activity and body warming;Whether the effectiveness of internet-supported cognitive behavioral therapy for insomnia can be augmented by simultaneous or prior application of bright light, physical activity and body warming; andWhether the effectiveness of the interventions and their combination are moderated by the insomnia subtype.

**Methods/Design:**

In a repeated measures, placebo-controlled, randomized clinical trial that included 160 people diagnosed with insomnia disorder, we are evaluating the relative effectiveness of 4 intervention weeks. Primary outcome is subjective sleep efficiency, quantified using a sleep diary. Secondary outcomes include other complaints of sleep and daytime functioning, health-related cost estimates and actigraphic objective sleep estimates. Compliance will be monitored both subjectively and objectively using activity, light and temperature sensors. Insomnia subtypes will be assessed using questionnaires. Mixed effect models will be used to evaluate intervention effects and moderation by insomnia subtype ratings.

**Discussion:**

The current study addresses multiple opportunities to optimize and personalize treatment of insomnia disorder.

**Trial registration:**

Netherlands National Trial Register NTR4010, 4 June 2013.

## Background

Dissatisfaction with sleep is reported by about 25 % of the adult Western population [1]. The prevalence is even higher in older people and twice as high in women as in men [2, 3]. When complaints about difficulties falling asleep, maintaining sleep, early morning awakenings or nonrestorative sleep are accompanied by physical or cognitive daytime complaints, and last for at least 3 months, occurring at least three times a week, without being secondary to environmental factors or comorbidities that prohibit sleep, a person suffers from insomnia disorder, according to the DSM-V [4]. These criteria are met by 6 to 10 % of adults [2]. Daytime complaints of people with insomnia concern cognitive functioning [5], depressed mood [6] and fatigue [6]. Additionally, people reporting insomnia or low sleep quality have higher risks of depression [7], metabolic diseases and cardiovascular problems [8]. These daytime consequences and comorbidities lead to a reduction in work productivity, to increased sick leave and healthcare consumption and consequently to high economic costs. In summary, insomnia has severe consequences for health and society [9], underscoring the importance of optimizing interventions to promote better sleep. To do so, the regulation of sleep needs to be considered.

### Circadian rhythm and sleep

Virtually all behavioral and physiological processes show a 24-h rhythm even in the absence of environmental time cues. This circadian (from circa = about, and dies = day) rhythm is, for example, present in sleep and wakefulness, hormone secretion, alertness, body temperature, metabolism, perception and cognition. Endogenous clock mechanisms that promote the expression of 24-h rhythms are located in all human cells [10] and are synchronized by the central clock of the brain, the hypothalamic suprachiasmatic nuclei (SCN). The SCN is considered the major clock because only SCN tissue is able to maintain a circadian rhythm in the absence of external input [10]. Under normal circumstances, several exogenous cues, or zeitgebers, entrain the SCN. Light is the strongest zeitgeber [11]. The retinohypothalamic tract (RHT) is one of the three major input pathways of the SCN, providing it with information from photoreceptor cells in the retina. Secondary zeitgebers include, for example, the temperature of the environment, body core and skin; metabolism; and the rest-activity cycle. When the circadian rhythms of the body are synchronized with the zeitgebers, the rhythm is optimally entrained. A type of insomnia that is characterized mostly by complaints about initiating sleep may be due to a misalignment of the circadian rhythm in sleep-promoting physiology and the sleep window the patient tries to adhere to, typically between 23:00 and 7:00 [12, 13].

### Homeostasis of sleep

In addition to the circadian regulation of sleep and wake, a homeostatic component affects sleep propensity. Whereas the circadian process is relatively independent of prior sleep or wake, the homeostatic process on the other hand is sensitive to the sleep-wake history [14]. The sleep homeostatic process increases sleep propensity during wakefulness until sleep is initiated. Sleep propensity declines during sleep. The biological mechanisms underlying sleep homeostasis are less well characterized than the mechanisms underlying circadian regulation, but likely involve astrocyte-dependent adenosine accumulation [15, 16].

Some types of insomnia may involve altered homeostatic regulation of sleep propensity [17].

### Sleep-permissive and wake-promoting conditions

Although the regulation of sleep and wakefulness has been well modeled by interacting circadian and homeostatic processes in lab studies, additional sleep-permissive and wake-promoting conditions have been largely overlooked [18]. Most people sleep best lying in bed, with the lights off and the curtains drawn, in a thermally agreeable, safe and relatively quiet environment. These parameters (posture, temperature, environmental light and sound, fear) moderate the expression of sleep and wake. Whether altered sensitivity to sleep-permissive and wake-promoting conditions might be involved in the sleep complaints of some types of insomnia remains virtually unexplored [19–21].

### Treatment of insomnia

Even though the underlying causes of insomnia are at present insufficiently understood, one of the most common treatments provided by primary caregivers (mainly general practitioners) is sedative or hypnotic drugs mostly benzodiazepines or benzodiazepine receptor antagonists [1]. Unfortunately, pharmacological treatments have a high prevalence of adverse effects. Daytime drowsiness, risk of abuse and addiction, and rebound insomnia on withdrawal are a few examples of these side effects [22]. Pharmacological treatment is therefore not recommended [23].

In the past decades, two other interventions have been developed. The first intervention is cognitive behavioral therapy for insomnia (CBT-I). It has similar or even better and more prolonged outcomes than pharmacological treatment, and lacks the negative side effects [24]. A second, less evolved, but promising type of intervention is chronobiological treatment (CT). Chronobiological treatments aim to enhance regular and appropriately timed input to the circadian timing system to support its role in sleep regulation, by use of bright light, body warming or physical activity (for example, [21, 25, 26], for a review see [27]). These manipulations may become more important with increasing age, to counteract age-related changes in the functional neuroanatomy of the biological clock of the brain [28].

### Cognitive behavioral therapy

Cognitive behavioral therapy for insomnia (CBT-I) is a combination of cognitive and behavioral treatments. CBT-I usually includes stimulus control (that is, association of bed with sleeping), sleep restriction (that is, restrict an individual’s time in bed to average sleep time), relaxation training, cognitive therapy (that is, diminish misconceptions about sleep) and sleep hygiene (for example, general guidelines about behavioral and environmental factors that influence sleep) [29]. CBT-I has been shown to be effective in numerous randomized clinical trials [24, 29–34]. A problem facing implementation on a large scale is the lack of skilled therapists.

### Chronobiological treatment

Three chronobiological manipulations have been applied successfully and will be discussed below.

#### Bright Light (BL)

Bright light, including natural daylight, entrains the circadian rhythm [35]. Retinal ganglion cells projecting to the SCN through the retinohypothalamic tract (RHT) inform the circadian timing system about the intensity of light exposure. The SCN uses this information to entrain its intrinsic rhythmic activity to the 24-h light–dark cycle [10]. Studies in humans show that phase shifts can be imposed by manipulation of the light–dark cycle [35, 36]. A phase advance can be induced by means of bright light given in the morning, especially closely after the body core temperature minimum; a phase delay can be induced with light applied in the interval from late afternoon to just prior to the body core temperature maximum [35, 37, 38]. The effect of light on sleep may not be limited to changing the sleep phase, as suggested by studies that found enhanced sleep quality in the absence of clear rhythm shifts [25, 39].

#### Body and skin warming (BW)

Core body temperature shows a clear 24-h rhythm. In normal sleepers with a sleep period between 23:00 and 7:00, the temperature peaks between 18:00 and 20:00 h and has its minimum between 4:00 and 5:00 h [11]. Apparently, the connection between sleep or vigilance and core body temperature is strong. We sleep when core body temperature is low and are awake when it is high [18]. In contrast, skin temperature is increased during the sleep period because of increased skin blood flow in response to a supine posture [40]. Increased skin blood flow promotes heat loss, resulting in a lower core body temperature. Romeijn *et al*. [18] reviewed the effect of manipulation of skin temperature on vigilance, and they explain in more detail the underlying processes. Several studies that applied water-perfused thermo suits to increase skin temperature slightly within the thermoneutral zone showed that this manipulation enhances sleep propensity [18]. This effect has not only been demonstrated in healthy adults, but also in people with insomnia [20, 21]. A more practical and home-applicable version of this temperature manipulation is to make use of the body’s thermoregulatory mechanisms and warm the body prior to sleep by mild physical activity or taking a hot bath [41]. About two hours later, core body temperature has returned to baseline, while skin temperature is still somewhat elevated. This pre-sleep body warming approach has been used with success in insomnia [42].

#### Physical Activity (PA)

As diurnal mammals, humans are active during the day and sleep at night. The rest-activity profile of people with a very inactive lifestyle, for example sedentary elderly, shows a small 24-h amplitude. Several studies evaluated the effect of enhancing physical activity or exercising on this amplitude and on sleep [26, 43–51]. Two possible mechanisms have been proposed to be involved in the effect of enhanced physical activity on sleep. The thermoregulatory hypothesis proposes that exercise exerts an effect on sleep through initially increasing core body temperature. This subsequently triggers heat loss to decrease the temperature, which is conducive to sleep. The body restoration hypothesis proposes that exercise depletes energy levels and promotes sleep because it increases the need to activate restorative mechanisms. In 2000, Driver & Taylor reviewed the studies done up until that year [46]. Unfortunately, most studies use good sleepers. Their conclusion was that exercise of moderate intensity and focusing on endurance rather than peak intensity, was most beneficial for perceived sleep quality. Tanaka *et al*. [51] showed that exercise is most effective around 17:00 h, supporting the thermoregulatory hypothesis. Benloucif *et al*. [43] however found equal effects of morning and evening exercise on subjective sleep quality. More recently, Passos *et al*. [50] summarized studies using exercise in primary insomnia. This review demonstrated improvement in sleep quality. Additionally, they discuss possible explanations for the acute and chronic effects of physical activity on primary insomnia [50].

### Optimizing treatment and accessibility

Whereas the combination of CT and CBT-I may be more effective than their use in isolation, and has successfully been applied in only one study [30, 52], no prior study addressed the relative contribution of the different interventions. More research is therefore needed to compare effectiveness of different combinations of therapies; one of the aims of the present study.

A problem facing implementation of CBT-I is the shortage of skilled therapists. Internet-based CBT-I may alleviate this problem [53]. Internet-based therapy is highly self-guided, structured and personalized. Knowledge-based technology renders a personalized concept consult, which can be adjusted by therapist for situations that cannot be pre-programmed. This saves a lot of time for a therapist and subsequently may help to solve the discrepancy between care needed and care available [33, 34], thus allowing for large-scale implementation.

Another opportunity for the optimization of treatment is based on the idea that the people suffering from insomnia most likely represent a heterogeneous mix of subtypes, with different underlying causes and expected treatment response. These subtypes may not only be distinguished by type of sleep problems. Other factors such as personality traits, medical complaints and medical history, the ability to perceive comfort [21, 54–56] may represent variables that differ between the proposed subtypes as well. Our research group commenced a large-scale study using web-based assessment of questionnaires to collect data on these variables (the Netherlands Sleep Registry, NSR, www.sleepregistry.org). The use of latent class analysis on these data will allow for the data-driven detection of multivariate subtypes, calculation of subtype probability for participants according to this data-driven subtype nosology, and evaluation of differential treatment responses, depending on the subtype probability.

The present study aims to evaluate the possibility to optimize insomnia treatment along the principles of personalized and stratified medicine, by making the first step towards the development of a protocol for individualized optimal treatment for specific subtypes of insomnia, which each may show different responsiveness to CBT-I and the different CT manipulations.

### Objectives

The objectives of this study are as follows:

1. To evaluate the relative effectiveness of internet-based CBT-I, three different types of CT (light, temperature and physical activity), and the combined application of CBT-I and each of the CT’s, as compared to placebo treatment, on [1] subjective sleep efficiency (primary outcome), [2] subjective daytime functioning, [3] actigraphic sleep estimates, and [4] cost effectiveness.

2. To evaluate whether insomnia subtype moderates the effectiveness of the individual and the combined treatments.

3. To evaluate whether the effect of CBT-I is enhanced by prior CT.

## Methods/Design

### Trial design

The study is a double blind, randomized, placebo controlled trial. Aiming at 160 participants who complete the trial, with a dropout rate of 10 %, 180 participants will be recruited, who will be randomly assigned to one of eight limbs in a repeated measures design with two factors (CBT-I and CT), of respectively 2 levels (active CBT-I treatment versus waitlist monitoring) and 4 levels (light, physical activity, body warming and placebo) (see Fig. 1). Covariate-adaptive randomization aims at an equal representation of insomnia subtypes within each treatment limb. Assessment will be performed at baseline (week 0), after a 4-week treatment period (week 5), and after a second 4-week treatment/monitoring period (week 10).

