### Randomization

Participants who meet the criteria and sign informed consent will be randomly assigned to CBT-I or to the waitlist and to one of the four CT conditions (including one placebo). Simple randomization will be applied to the first batch of 48 participants. During the staggered entry of subsequent participants, covariate-adaptive randomization [61] will be applied in order to maintain balanced groups throughout the study. The covariates are age, sex, use of non-sleep related medication and time of year. Since some covariates are continuous rather than categorical, randomization will be done following the method proposed by Frane [62]. This method temporarily assigns each new participant one by one to each treatment group and obtains a *P* value of the test for between-group differences for each of the covariates for that assignment, using analysis of variance (ANOVA) for continuous variables and a X^2^ test for categorical variables. This renders a *P* value for each of the four covariates for each of the eight possible assignments. The lowest of the four *P* values thus represents the least balanced covariate in that assignment situation. These lowest, or minimum, *P* values per assignment will then be used to make the actual assignment to one of the treatment conditions, where a participant will be assigned to the group for which this minimum *P* value is highest, thus resulting in a group assignment that keeps imbalance over groups as small as possible. If group sizes become unbalanced (that is, differing by more than five participants), the Frane method will be applied only to the six smallest groups instead of all eight. All randomization will be done using R [63]. Randomization will be scripted, so actual group assignment is automated.

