### Effect moderation by subtype score

Preliminary results of the Latent Class Analysis on comprehensive psychometric data of a large sample of participants of the Netherlands Sleep Registry suggests the existence of four different subtypes of insomnia, each with about equal prevalence. From the extensive number of questionnaires on traits these volunteers filled out, we are presently selecting the minimal subset of questions required to obtain good estimates of the a posteriori probabilities of a participant to belong to each one of the four classes. These items will be included in a Sleep Subtype Survey that will be assessed in all participants of the present RCT. The resulting four Insomnia Subtype Probabilities (ISP) will be included in analyses aimed at evaluating treatment effect moderation by each of the four insomnia subtype probabilities.

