#### Treatment effects and moderation estimates

Mixed effect models will be applied to estimate all time by treatment effects, time by treatment interaction effects and effect moderation by the individual’s insomnia subtype probabilities. For each outcome measure, all effects will be estimated simultaneously in one single linear regression equation. The primary outcome measure of sleep efficiency will be illustrated below. The diary and actigraphy based outcome measures have a two-level hierarchical data-structure: repeated measures of 14 diary inputs *i* across T0 and T1 are nested within subjects *j*. The 14*160 = 2,240 data points can be used to estimate simultaneously all effects ß using the following mixed effect model:$$ \begin{array}{l}\mathrm{S}{\mathrm{E}}_{\mathrm{ij}}\kern0.5em =\kern0.5em {\mathrm{\ss}}_{0\mathrm{i}\mathrm{j}}\kern0.5em +\kern0.5em {\mathrm{\ss}}_1*{\mathrm{Time}}_{\mathrm{ij}}\kern0.5em +\kern0.5em {\mathrm{\ss}}_2*\mathrm{C}\mathrm{B}\mathrm{T}\hbox{-} {\mathrm{I}}_{\mathrm{j}}\kern0.5em +\kern0.5em {\mathrm{\ss}}_3*\mathrm{B}{\mathrm{L}}_{\mathrm{j}}\kern0.5em +\kern0.5em {\mathrm{\ss}}_4*\mathrm{P}{\mathrm{A}}_{\mathrm{j}}\kern0.5em +\kern0.5em {\mathrm{\ss}}_5*\mathrm{B}{\mathrm{W}}_{\mathrm{j}}\kern0.5em +\kern0.5em {\mathrm{\ss}}_6*\mathrm{IS}{\mathrm{P}}_{\mathrm{j}}\kern0.5em +\kern0.5em {\mathrm{\ss}}_7*\mathrm{T}\mathrm{i}\mathrm{m}{\mathrm{e}}_{\mathrm{ij}}*\mathrm{IS}{\mathrm{P}}_{\mathrm{j}}+\\ {}\kern0.5em {\mathbf{\ss}}_{\mathbf{8}}*\mathbf{C}\mathbf{B}\mathbf{T}\hbox{-} {\mathbf{I}}_{\mathbf{j}}*\mathbf{T}\mathbf{i}\mathbf{m}{\mathbf{e}}_{\mathbf{ij}}\kern0.5em +\kern0.5em {\mathrm{\ss}}_9*\mathrm{C}\mathrm{B}\mathrm{T}\hbox{-} \mathrm{I}*\mathrm{IS}{\mathrm{P}}_{\mathrm{j}}\kern0.5em +\kern0.5em {\mathbf{\ss}}_{\mathbf{10}}*\mathbf{C}\mathbf{B}\mathbf{T}\mathbf{\hbox{-} }{\mathbf{I}}_{\mathbf{j}}*\mathbf{T}\mathbf{i}\mathbf{m}{\mathbf{e}}_{\mathbf{ij}}*\mathbf{I}\mathbf{S}\mathbf{P}+\\ {}\kern0.5em {\mathbf{\ss}}_{\mathbf{11}}*\mathbf{B}{\mathbf{L}}_{\mathbf{j}}*\mathbf{T}\mathbf{i}\mathbf{m}{\mathbf{e}}_{\mathbf{ij}}\kern0.5em +\kern0.5em {\mathrm{\ss}}_{12}*\mathrm{B}\mathrm{L}*\mathrm{IS}{\mathrm{P}}_{\mathrm{j}}\kern0.5em +\kern0.5em {\mathbf{\ss}}_{\mathbf{13}}*\mathbf{B}{\mathbf{L}}_{\mathbf{j}}*\mathbf{T}\mathbf{i}\mathbf{m}{\mathbf{e}}_{\mathbf{ij}}*\mathbf{I}\mathbf{S}{\mathbf{P}}_{\mathbf{j}}+\\ {}\kern0.5em {\mathbf{\ss}}_{\mathbf{14}}*\mathbf{P}{\mathbf{A}}_{\mathbf{j}}*\mathbf{T}\mathbf{i}\mathbf{m}{\mathbf{e}}_{\mathbf{ij}}\kern0.5em +\kern0.5em {\mathrm{\ss}}_{15}*\mathrm{P}\mathrm{A}*\mathrm{IS}{\mathrm{P}}_{\mathrm{j}}\kern0.5em +\kern0.5em {\mathbf{\ss}}_{\mathbf{16}}*\mathbf{P}{\mathbf{A}}_{\mathbf{j}}*\mathbf{T}\mathbf{i}\mathbf{m}{\mathbf{e}}_{\mathbf{ij}}*\mathbf{I}\mathbf{S}{\mathbf{P}}_{\mathbf{j}}+\\ {}\kern0.5em {\mathbf{\ss}}_{\mathbf{17}}*\mathbf{B}{\mathbf{W}}_{\mathbf{j}}*\mathbf{T}\mathbf{i}\mathbf{m}{\mathbf{e}}_{\mathbf{ij}}\kern0.5em +\kern0.5em {\mathrm{\ss}}_{18}*\mathrm{B}\mathrm{W}*\mathrm{IS}{\mathrm{P}}_{\mathrm{j}}\kern0.5em +\kern0.5em {\mathbf{\ss}}_{\mathbf{19}}*\mathbf{B}{\mathbf{W}}_{\mathbf{j}}*\mathbf{T}\mathbf{i}\mathbf{m}{\mathbf{e}}_{\mathbf{ij}}*\mathbf{I}\mathbf{S}{\mathbf{P}}_{\mathbf{j}}+\\ {}\kern0.5em {\mathrm{\ss}}_{20}*\mathrm{C}\mathrm{B}\mathrm{T}\hbox{-} {\mathrm{I}}_{\mathrm{j}}*\mathrm{B}{\mathrm{L}}_{\mathrm{j}}\kern0.5em +\kern0.5em {\mathbf{\ss}}_{\mathbf{21}}*\mathbf{C}\mathbf{B}\mathbf{T}\mathbf{\hbox{-} }{\mathbf{I}}_{\mathbf{j}}*\mathbf{B}{\mathbf{L}}_{\mathbf{j}}*\mathbf{T}\mathbf{i}\mathbf{m}{\mathbf{e}}_{\mathbf{ij}}\kern0.5em +\kern0.5em {\mathrm{\ss}}_{22}*\mathrm{C}\mathrm{B}\mathrm{T}\hbox{-} {\mathrm{I}}_{\mathrm{j}}*\mathrm{B}{\mathrm{L}}_{\mathrm{j}}*\mathrm{IS}{\mathrm{P}}_{\mathrm{j}}\kern0.5em +\kern0.5em {\mathbf{\ss}}_{\mathbf{23}}*\mathbf{C}\mathbf{B}\mathbf{T}\hbox{-} \\ {}\kern0.5em {\mathbf{I}}_{\mathbf{j}}*\mathbf{B}{\mathbf{L}}_{\mathbf{j}}*\mathbf{T}\mathbf{i}\mathbf{m}{\mathbf{e}}_{\mathbf{ij}}*\mathbf{I}\mathbf{S}\mathbf{P}+\\ {}\kern0.5em {\mathrm{\ss}}_{24}*\mathrm{C}\mathrm{B}\mathrm{T}\hbox{-} {\mathrm{I}}_{\mathrm{j}}*\mathrm{P}{\mathrm{A}}_{\mathrm{j}}\kern0.5em +\kern0.5em {\mathbf{\ss}}_{\mathbf{25}}*\mathbf{C}\mathbf{B}\mathbf{T}\mathbf{\hbox{-} }{\mathbf{I}}_{\mathbf{j}}*\mathbf{P}{\mathbf{A}}_{\mathbf{j}}*\mathbf{T}\mathbf{i}\mathbf{m}{\mathbf{e}}_{\mathbf{ij}}\kern0.5em +\kern0.5em {\mathrm{\ss}}_{26}*\mathrm{C}\mathrm{B}\mathrm{T}\hbox{-} {\mathrm{I}}_{\mathrm{j}}*\mathrm{P}{\mathrm{A}}_{\mathrm{j}}*\mathrm{IS}{\mathrm{P}}_{\mathrm{j}}\kern0.5em +\kern0.5em {\mathbf{\ss}}_{\mathbf{27}}*\mathbf{C}\mathbf{B}\mathbf{T}\mathbf{\hbox{-}}\\ {}\kern0.5em {\mathbf{I}}_{\mathbf{j}}*\mathbf{P}{\mathbf{A}}_{\mathbf{j}}*\mathbf{T}\mathbf{i}\mathbf{m}{\mathbf{e}}_{\mathbf{ij}}*\mathbf{I}\mathbf{S}\mathbf{P}\mathbf{j}+\\ {}\kern0.5em {\mathrm{\ss}}_{28}*\mathrm{C}\mathrm{B}\mathrm{T}\hbox{-} {\mathrm{I}}_{\mathrm{j}}*\mathrm{B}{\mathrm{W}}_{\mathrm{j}}\kern0.5em +\kern0.5em {\mathbf{\ss}}_{\mathbf{29}}*\mathbf{C}\mathbf{B}\mathbf{T}\mathbf{\hbox{-} }{\mathbf{I}}_{\mathbf{j}}*\mathbf{B}{\mathbf{W}}_{\mathbf{j}}*\mathbf{T}\mathbf{i}\mathbf{m}{\mathbf{e}}_{\mathbf{ij}}\kern0.5em +{\mathrm{\ss}}_{30}*\mathrm{C}\mathrm{B}\mathrm{T}\hbox{-} {\mathrm{I}}_{\mathrm{j}}*\mathrm{B}{\mathrm{W}}_{\mathrm{j}}*\mathrm{IS}{\mathrm{P}}_{\mathrm{j}}\kern0.5em +\kern0.5em {\mathbf{\ss}}_{\mathbf{31}}*\mathbf{C}\mathbf{B}\mathbf{T}\mathbf{\hbox{-}}\\ {}\kern0.5em {\mathbf{I}}_{\mathbf{j}}*\mathbf{B}{\mathbf{W}}_{\mathbf{j}}*\mathbf{T}\mathbf{i}\mathbf{m}{\mathbf{e}}_{\mathbf{ij}}*\mathbf{I}\mathbf{S}{\mathbf{P}}_{\mathbf{j}}\end{array} $$

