## Trial status

Recruitment started in October 2013 and is ongoing. In January 2014, the first participants enrolled. Currently, 60 participants have completed the protocol.

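### Adaptive randomisation is said to balance insomnia subtype but balances four other variables, and the specified model leaves those four out

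*Protocol article*

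**What the plan says.** Trial design gives the purpose of the allocation method: "Covariate-adaptive randomization aims at an equal representation of insomnia subtypes within each treatment limb".

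The Randomization section describes the method. It begins: "Simple randomization will be applied to the first batch of 48 participants". After that batch, each newcomer is tried in every limb and placed where the worst-balanced covariate is least unbalanced. The section lists what is balanced: "The covariates are age, sex, use of non-sleep related medication and time of year". The list is closed, because the algorithm computes a P "value for each of the four covariates for each of the eight possible assignments". Subtype is not on it.

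Effect moderation by subtype score says of the survey that will yield the four insomnia subtype probabilities (ISPs): "we are presently selecting the minimal subset of questions required to obtain good estimates of the a posteriori probabilities". Trial status says: "Currently, 60 participants have completed the protocol".

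Treatment effects and moderation estimates fixes the analysis: "For each outcome measure, all effects will be estimated simultaneously in one single linear regression equation". The equation contains Time, CBT-I, BL, PA, BW, one ISP and their products, with coefficients 1 to 31. The one simplification declared is that three further ISPs are not shown. Age, sex, medication and time of year do not appear.

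**The concern.** Subtype is the moderator in objective 2. A reader of Trial design would conclude that its spread over the eight limbs is controlled by design, while the Randomization section shows that it is not. A thin subtype in a limb widens the interval for any moderation effect that depends on that limb.

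The second issue runs the other way. Four variables do steer allocation, but the model ignores them. Balancing on a variable that predicts the outcome makes the treatment contrast less variable than an unadjusted model assumes. The model's standard errors are then too large, and precision that the design has paid for is not used.

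**Working it through.** **1. The plan's own figures.** Inputs from Power and sample size: 160 completers, ICC 0.27, T = 7 nights per assessment, power 0.80, alpha 0.05 (taken as two-sided, which reproduces the figures). With r = n2/n1,

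d = √[(1.96 + 0.842)² (r + 1)(1 + 6 × 0.27) / (n1 × r × 7)].

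| Effect | Split | Computed | Stated |
|---|---|---|---|
| CBT-I | 80/80 | 0.271 | 0.27 |
| Each CT | 40/120 | 0.313 | 0.31 |
| CBT-I by CT | 20/140 | 0.410 | 0.41 |
| CT versus CT | 40/40 | 0.383 | 0.38 |
| Subtype by CBT-I | 40/120 | 0.313 | 0.31 |
| Subtype by CT | 20/140 | 0.410 | 0.41 |
| Subtype by CT versus CT | 20/60 | 0.443 | 0.44 |
| Subtype by combined | 10/150 | 0.560 | 0.55 |

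The figures reproduce, apart from a trivial difference in the last. The last row is the relevant one: 160/8 = 20 per limb, and the median split is taken to fall evenly inside the limb, giving 10.

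**2. Allocation without the final survey.** At least 60 of the planned 160 (38%) were allocated before the item set existed. At most 48 of those 60 can belong to the simply randomised batch. So at least 60 − 48 = 12 completers were allocated by the adaptive algorithm without the final subtype score.

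**3. Cost of leaving subtype to chance.** Assume, for illustration, a yes/no subtype with 25% prevalence (the article expects four subtypes about equally common) and simple randomisation. The variance of a subtype-by-treatment contrast is proportional to the sum over groups of 1/n(subtype) + 1/n(other). With perfect balance and four limbs of 20, this is 4 × (1/5 + 1/15) = 1.067. Simulated counts against the perfectly balanced value give:

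| Contrast | Groups | Mean increase in SE |
|---|---|---|
| CBT-I | 80/80 | 1.5% |
| Each CT | 40/120 | 2.5% |
| CT versus CT | 40/40 | 3.2% |
| CBT-I by CT | four limbs of 20 | about 7.5% (95th percentile about 33%) |

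For the last row, the roughly 1% of draws with an empty cell were excluded from the mean.

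**4. Cost of omitting the balancing covariates.** Let R² be the share of the variance of the change that the four variables explain. The documents give no value, so it is assumed. With perfect balance, the SE is overstated by 1/√(1 − R²), and the true level is 2[1 − Φ(1.96/√(1 − R²))].

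- R² = 5%: SE factor 1/√0.95 = 1.026; level 4.4%; power 0.81 unadjusted, 0.82 adjusted.
- R² = 10%: SE factor 1/√0.90 = 1.054; level 3.9%; power 0.81 unadjusted, 0.84 adjusted.

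These are upper bounds on the distortion, because balance is imperfect and the first 48 are simply randomised.

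**5. Is 5 to 10% a sensible range?** Set total variance to 1. Night-to-night noise contributes 2 × 0.73/7 = 0.21 to the variance of a participant's change, and baseline variables cannot explain it. Suppose true differences in change have variance 0.05, 0.10 or 0.20, and the covariates explain 20% of that (all assumed). Then R² = 0.01/0.259 = 4%, 0.02/0.309 = 6%, or 0.04/0.409 = 10%.

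**The case against.** **The equation is only an illustration.** The article introduces it as one, shows a single ISP for clarity, and may leave adjustment to a plan not at hand. This carries some weight. But the equation is set out term by term, the article says all effects come from that one equation, and the only omission it declares concerns the ISPs.

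**The covariates hardly matter for within-person contrasts.** This largely stands. Every effect of interest contains Time, so age, sex, medication and season count only as far as they predict change. The loss is probably small.

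**Thin cells look worse than they are.** With limbs of 20, a given subtype has two or fewer members with probability 0.091 (binomial, 20 and 0.25), or 2.9 of 32 limb-by-subtype cells. Simulation puts the chance of at least one such cell at 97%. A reader might infer that objective 2 is badly compromised. That does not follow. The plan models continuous probabilities, not classes, and its power work pools limbs for all but the combined moderation.

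**Imbalance could bias the moderation estimates.** A reader might infer this too, but it is not supported. Nothing suggests that allocation depends on subtype given the covariates used, and the model carries ISP terms.

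**The moderator was measured after treatment in the 60 completers.** This is possible but not shown. The items come from trait questionnaires that registry volunteers had already filled out, and part of the sample is recruited from that registry. Others come through media, and the article does not say when the completers answered.

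**Conclusion.** The two sections contradict each other: the design is credited with a property that its algorithm does not have and that could not have been applied with the final survey for at least 60 participants. Chance subtype spread causes no bias and costs roughly 1.5 to 3% in standard error for the pooled moderation contrasts. The combined CBT-I by CT moderation is the exposed one, at about 7.5% on average, and its detectable effect is already the largest in the plan (d = 0.55). These sizes assume a 25% binary subtype and limbs of 20.

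The omitted covariates make the Time-by-treatment tests slightly conservative. At an assumed R² of 5 to 10%, standard errors are at most 3 to 5% too large and the level is 4.4 to 3.9% instead of 5%. A stronger reading, with R² of 20%, SEs 12% too large and a level of 2.8%, sits poorly with the night-to-night noise implied by the ICC of 0.27. This omission gives no ground for concern about false positives.

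**What to change.** 1. Correct the Trial design sentence to the four covariates actually used. Alternatively, once the survey is final, add the ISPs to the allocation script for participants still to be assigned, and state from which participant on. Cost: one sentence, or one script change.
2. Add age, sex, non-sleep medication and time of year to the model, each with its product with Time. Main effects alone would not change the Time-by-treatment contrasts. Cost: eight parameters if each variable takes one column, a few more if time of year needs two.
3. State when the subtype items were answered relative to the start of treatment. If any participants answered afterwards, repeat the moderation analysis without them. Cost: one sentence and, if needed, one sensitivity analysis.
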